#### **6.6.4 Other medications**

Participants taking other medications that might require adjustment during the intervention period, such as oral anti-glycaemics and anti-hypertensives, will be assessed by the study physician via a Telehealth Medical Assessment prior to the commencement of the intervention period, who will develop an individual medication management plan (Attachment 9). The purpose of this plan is for the study physician to flag any potential medication adjustments with participants' usual HCP and usual GP (unless this is the same practitioner). The study physician may also recommend the participant do additional self-monitoring (e.g., measure blood pressure once daily) to help guide any medication adjustments that may be needed. It is then ultimately up to participants' usual GP to make the decision on what precise medication adjustments are required, if any, throughout the study. The participant will be asked to report any medication changes to the study dietitian at each fortnightly diet session throughout the study so they can be recorded. Any medication change will be flagged with the study physician and a medical review will be scheduled if necessary, or the study physician will contact participants' usual GP to discuss the change(s).

If consent is provided by the participant, GPs will be notified of their patient's involvement in the study upon recruitment of the participant (their patient) and will be provided with a letter outlining study information (Attachment 53). The involvement of participants' usual GPs is not expected to place a significant increased burden on these practitioners because it is their duty of care to review and adjust medications for their patients on a regular basis, particularly when diet change is undertaken. The expected adjustments include reductions in or changes to anti-hypertensive and anti-hyperglycaemic medications [24]. The study physician and study endocrinologist will be available to consult with participants' usual GPs, if needed. Participants will be encouraged to continue following up with their usual GP for general medical issues and enquiries.

#### **6.6.5 Physical activity**

All participants will be encouraged to maintain their usual physical activity level throughout the entire duration of the study.

#### **6.6.6 Outcome measurements (post-intervention)**

During the last week of the intervention period (week 16), participants will be required to have their outcomes measured seven days apart. All health outcome measurements will be collected following the same procedures outlined in the control period. See Table 1 and Figure 1 for a detailed schedule of what outcomes will be measured and when throughout the entire study.

### **6.7 Follow Up**

The end of the intervention period will mark the end of the active education period. However, participants will be asked to schedule one final follow-up Telehealth session with [name] after another 12 weeks for the purposes of collecting follow-up outcome data (Figure 1). The purpose of this part of the study is to assess what dietary approach participants choose to take after the LC diet intervention, and then as a consequence of this – what is the impact of their diet on their HbA1c, quality of life and diet satisfaction. There will be no scheduled contact with the study dietitian, study physician or study diabetes educator during the follow-up period. Participants will be advised to follow up with their usual diabetes care team for all matters, as they were doing prior to entering the study. It will be the sole decision of the participants as to whether or not they continue to follow the LC diet. Participants will be able to keep all the resources that were provided to them throughout the course of the study.

Participants will be sent a reminder email two weeks prior to the scheduled session which will include relevant instructions. The only outcome data being measured at follow-up is HbA1c (collected at Australian Clinical Labs using a pre-paid form from iMedical), dietary intake (collected by the study dietitian using a 24-hour diet recall), total daily insulin dose (collected by participants using a 24-hour insulin logbook), quality of life (collected by participants using the DQOL Brief Clinical Inventory) [25] and diet satisfaction (collected by participants using a validated questionnaire [26]). Participants will be provided with a link to a follow-up survey hosted on REDCap where they can securely record and upload their follow-up data.

### **6.8 Schedule of events**

The schedule of events from first contact to follow-up (final contact) is displayed in Figure 1. Participants will be sent text message reminders by [name] the day before action is required from them (e.g., attend pathology collection centre, telehealth diet sessions).

### **6.9 Withdrawal / termination**

Withdrawal from the study will be possible at any time and only data collected about the withdrawing participant up until that point will be included in the study. Participants will be asked for their reason(s) for withdrawing but will be under no obligation to answer. The date of withdrawal and reason for withdrawing (if provided) will be recorded in REDCap. There will be no consequences for withdrawing from the study.

Although unlikely, serious safety concerns may lead the researchers to terminate individual participation in the study or terminate the study entirely. For example, if a participant were to suffer a serious adverse event that was directly attributed to the study intervention. With consideration that the nature of this study is to investigate the effect(s) of a dietary intervention with a high level of professional support, we expect the risk of any adverse events to be minimal.

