## 6. RESEARCH PLAN / STUDY DESIGN

### 6.1 Type of study

A 28-week single arm, within-participant controlled intervention study.

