### 6.2 Population / sample size

The primary outcome is HbA1c. Based on a clinically relevant difference in HbA1c of 0.7% (absolute) with a standard deviation of 1.0 [17], to achieve 80% power with  $\alpha < 0.05$ , we require a sample size of  $n=16$ . Anticipating a 20% dropout rate, we plan to recruit 20 participants into the study.

However, as this study is part of a PhD project, we've only got time and resourcing to have a recruitment period of 5 months. The recruitment period will end at 5 months and the study will continue, irrespective of the number of participants recruited up until that point (Table 2).

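### Section 6.9 does not separate stopping the diet from leaving the study, so anyone who leaves during the intervention has no HbA1c after starting the diet, and the week 4 to week 16 change is open to attrition bias

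*Protocol*

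**What the plan says.** Protocol section 6.9 allows withdrawal from the study at any time and adds that "only data collected about the withdrawing participant up until that point will be included in the study". The date, and the reason if one is offered, are recorded. For removal by the researchers it says that "serious safety concerns may lead the researchers to terminate individual participation in the study", and its example is a serious adverse event attributed to the intervention. Neither sentence mentions a person who stops the diet but remains available for measurement.

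Section 6.1 describes the design: "A 28-week single arm, within-participant controlled intervention study". Section 6.2 says "The primary outcome is HbA1c", sizes the study on a "clinically relevant difference in HbA1c of 0.7% (absolute) with a standard deviation of 1.0", and continues: "Anticipating a 20% dropout rate, we plan to recruit 20 participants into the study". It attaches no cause or timing to that 20%.

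Table 1 places blood draws at the end of week 0, the end of week 4, the end of week 16 and shortly before the follow-up session at the end of week 28. The diet begins on the day of the week 4 visit.

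Three other places bear on the point. Section 6.6.1 gives the example of a participant eating well above the prescribed carbohydrate, and the response is to renegotiate the prescription. Section 6.6.6 collects the week 16 outcomes without any adherence condition. Section 6.7 takes HbA1c at follow-up whatever diet the participant has chosen by then.

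**The concern.** The primary result is a within-person change with no concurrent comparator, so it depends on who still has a blood test at week 16. Leaving a demanding diet, or being taken off it for a safety event, is plausibly related to poor tolerance or poor glycaemic response. If those people have no value at week 16, the observed change leans towards those who did well.

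This has to be settled in the protocol. A statistical analysis plan can choose an analysis set or a missing-data method, but it cannot supply a blood test that was never taken. Data retained under 6.9 for someone who leaves during the intervention include only the two control-period HbA1c values, which say nothing about the effect of the diet.

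The follow-up has a similar but smaller gap. Section 6.7 states: "The purpose of this part of the study is to assess what dietary approach participants choose to take after the LC diet intervention". Participants who reach week 16 and then drop the diet are measured. Those who rejected it earlier and left the study are not.

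**Working it through.** **1. The plan's own numbers.** Inputs from section 6.2: difference 0.7, SD 1.0, power 80%, alpha 0.05 (taken as two-sided, since the side is not stated).

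- Paired change, normal approximation: n = (SD × (z₀.₉₇₅ + z₀.₈₀) / difference)² = (1.0 × (1.960 + 0.842) / 0.7)² = 16.02. The stated 16 reproduces, with power 0.7996 at n = 16.
- Dropout: 16 / (1 − 0.20) = 20, so the plan allows for 20 − 16 = 4 losses.

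**2. What a leaver contributes to HbA1c, from Table 1.**

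| Time of leaving the study | HbA1c before the diet | HbA1c after starting the diet |
|---|---|---|
| During the control period | week 0 only | not a diet starter |
| After the diet starts, before the week 16 draw | weeks 0 and 4 | none |
| After the week 16 draw | weeks 0 and 4 | week 16 |
| Stays in, poor adherence or off the diet | weeks 0 and 4 | weeks 16 and 28 |

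The second row is the gap. The fourth row shows that it arises from leaving the study, not from poor adherence.

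**3. Illustration of size.** The protocol gives no outcomes for leavers, so their change is assumed. Suppose that all 20 start the diet, L of them leave before week 16, those who remain change by −0.70 on average, and leavers change by c. The mean over all starters is ((20 − L) × (−0.70) + L × c) / 20.

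| L | c = 0 | c = +0.3 |
|---|---|---|
| 2 | −12.6 / 20 = −0.63 | (−12.6 + 0.6) / 20 = −0.60 |
| 4 | −11.2 / 20 = −0.56 | (−11.2 + 1.2) / 20 = −0.50 |
| 6 | −9.8 / 20 = −0.49 | (−9.8 + 1.8) / 20 = −0.40 |

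At the planned loss (L = 4) with no change in leavers, the result in those remaining exceeds the all-starter value by 0.70 − 0.56 = 0.14 points, a ratio of 0.70 / 0.56 = 1.25. Over the whole table the excess runs from 0.07 to 0.30 points.

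**4. Dependence on timing.** If 2 of the 4 losses fell in the control period, there would be 18 starters and 2 leavers: 16 × 0.70 / 18 = 0.62, an excess of 0.08. If all 4 fell in the control period, the change among starters would lose nobody. If leavers changed as much as those who stayed, the excess would be zero.

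**The case against.** The strongest reply is that section 6.9 is ordinary language protecting the right to withdraw. It governs withdrawal from the study and nowhere says that stopping or failing the diet counts as withdrawal. Sections 6.6.1, 6.6.6 and 6.7 keep non-adherent participants in and measure them. This stands. A reader might infer that someone who gives up the diet in week 8 must lack a week 16 HbA1c, or that the result will describe only people who tolerated the diet. The documents support neither: the value is lost only if the person also leaves or is removed.

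It is also fair to say that the 20% is a general allowance that may include losses in the control period, that some withdrawals will have nothing to do with the diet, and that no completers-only analysis is stated. Section 6.3 names an analysis of variance without an analysis set, which may properly be left to a statistical analysis plan that is not at hand. A reader might therefore take 25% as the expected overstatement. It is an illustration under assumptions that the protocol does not make.

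On safety, section 6.9 calls termination unlikely, and hypoglycaemia and ketone referrals are documented for safety reporting (sections 6.6.3, 7.3.2 and 7.3.4). The safety record is not lost.

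What the reply does not remove is the gap itself. Renegotiating a prescription is not the same as stopping, the follow-up reaches only people still in the study, and nothing tells the team to ask a person who stops the diet to come for the week 16 draw.

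**Conclusion.** The point holds as a weakness in a stated data-collection rule. Section 6.9 offers only exit from the study, and with no HbA1c drawn between weeks 4 and 16, each person who leaves or is removed in that interval is missing from the primary change. With no comparison arm and an allowance of 4 losses in 20, the estimate is exposed to attrition bias.

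The likely direction, in favour of the diet, rests on the assumption that leaving is related to poor tolerance, poor response or a safety event. The size cannot be known from the protocol. Under the assumptions shown it is 0.14 points at the planned loss and 0.07 to 0.30 points over the range tried, against a target of 0.7. It would be smaller if some losses precede the diet. The sample size is not affected by this point. The change should be made, because it is simple and the missing values cannot be recovered later.

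**What to change.** In section 6.9, and in the information sheet to match, distinguish two situations:

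- **Stopping the diet**, by choice or by researcher decision. The participant is asked to stay for the already scheduled week 16 HbA1c and questionnaires and for the week 28 follow-up, using the existing remote route.
- **Withdrawing consent to data collection.** Only this ends measurement, and the right to do so at any time is unchanged.

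An additional HbA1c at the moment of exit is not needed: a value at an arbitrary week is not a 12-week change. The choice of analysis set can be left to the statistical analysis plan. Nothing here alters any rule on when the diet is stopped.

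The cost is one paragraph, a few reminder contacts and a possibly less favourable HbA1c estimate. No draws are added, since the eligibility criteria already require willingness to attend four. The study costing is in an attachment that is not shown, so the budget effect could not be checked.

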### **6.10 Informed consent process**

Potential participants will be independently responsible for contacting the researchers to make initial contact and express their interest to participate in the study (via email, phone or completion of survey on REDCap to freely provide contact details). All participants will be required to complete the online survey hosted on REDCap which includes a downloadable PDF of the PIS. All potentially eligible participants will be required to provide their informed written consent by completing the online survey and ticking a box to confirm they have read the PIS and fully understand the study details.

### **6.11 Participant reimbursement**

There will be no reimbursements provided to participants for being involved in the study.

### **6.12 Continuation of therapy**

At the end of the study, participants will be advised to continue following up with their usual general practitioner and HCP(s) for all matters. Participants will be able to keep all the

resources provided to them throughout the intervention period and may wish to continue following the dietary intervention under the support of their usual HCP(s). Although [name], [name], [name] and [name] offer consultations in private practice, participation in this study does not necessarily allow for participants to remain clients of [name], [name], [name] or [name] when the study is finished. If, on completion of the study, participants wish to secure an appointment with [name], [name], [name] or [name], they will be responsible for organising this and paying any future consulting fees arising from these consultations.

### **6.13 Confidentiality and Privacy**

Participant information will be stored securely and kept strictly confidential, except as required by law. There will be no sharing of identifiable data with anyone not listed on this protocol, except for the participants' nominated HCP, without prior written consent from the participant. Refer to section 10 for full details on our data management plan, which is heavily focused on protecting participants' confidentiality and privacy at all times.

## **7. ETHICAL CONSIDERATIONS**

We will obtain ethics approval from the University of Sydney and will comply with all standards set by their human ethics committee.

### **7.1 Avoiding real or perceived coercion (recruitment)**

Our method of recruitment, as outlined in section 6.4, is via anonymous flyers and posters (distributed using multiple platforms), with all prospective patients reaching out to researchers. Therefore, there is no risk of real or perceived coercion in the recruitment process.

### **7.2 Privacy & confidentiality in the dissemination of research results**

The overall results of this research project will be disseminated via journal publication(s), conference presentations, educational seminars and a student thesis. Results will be primarily reported as means and variances; individuals will not be identifiable in any dissemination of research results. Where reference to individual data is appropriate/necessary, this will be reported as "one participant", etc. rather than using participant ID codes or any potentially identifying information.

## 7.3 Potential risks involved with participation in research

### 7.3.1 Discomfort or infection

There is a small risk of discomfort infection associated with finger-prick blood sampling, application of glucose monitoring devices, and venipuncture blood draws. In all cases, standard antiseptic protocols and procedures will be used to minimise the risk of physical harm. It should be noted that the expected physical harm from participating in this research is typical of standard T1D management. For example, regular finger pricks (for blood glucose and ketone testing) and insulin injections are required of all T1D patients, irrespective of their dietary management protocols. It is acknowledged that some patients may not be familiar with the use of a continuous or flash blood glucose monitoring (CGM or FGM) device, and in these cases, the study dietitian will take additional time to explain the risks/benefits and expectations of applying and wearing this device. The devices used are commercially available and will be used for their proposed purpose (<https://eshop.medtronic-diabetes.com.au/en/cgmsupplies/sensors>; <https://www.freestylelibre.com.au/freestyle-libre-au-sensor.html>).

### 7.3.2 Hypoglycaemia

Hypoglycaemia is a common acute complication of T1D which generally results from the difficulties in predicting expected rises in blood glucoses levels and accurately calculating insulin requirements. Due to the expected change(s) in insulin requirements as a result of the diet intervention, there is a risk of participants miscalculating their insulin requirements in the early stage of the intervention which could lead to increased frequency and/or severity of hypoglycemia. This will be mitigated by close monitoring of blood glucose levels, regular contact with the study dietitian, ongoing support from a nominated HCP, and oversight/supervision by the study physician, study diabetes educator and study endocrinologist.

Hypoglycaemia is defined by Diabetes Australia as a blood glucose level below 4 mmol/L [27]. The resources developed by the study dietitian and diabetes educator titled 'Managing hypoglycaemia' (Attachments 42 and 48) provide participants with information and guidelines on preventing and/or managing hypoglycaemia during the study. Participants will be required to test their blood glucose levels at least six times every day (i.e., before and 2 hours after each meal) using their own glucose monitoring

device, as per standard of care diabetes practice. They will also be encouraged to test their blood glucose levels before going to bed and before driving or participating in exercise. Participants will also be advised to test their glucose more often if they are: feeling sick or stressed; more or less physically active; experiencing more hypos than usual; experiencing changes in their routine; experiencing night sweats or morning headaches; noticing frequent instances of high blood glucose levels; and/or starting on new medications. Participants will be asked to provide their blood glucose data from their blood glucose monitoring device to the dietitian for review every fortnight throughout the study. If using a CGM or flash glucose monitor (FGM), any reading(s)  $<4$  mmol/L should be confirmed with a finger prick device. If two or more readings across a 14-day period are  $<4.0$  mmol/L then the dietitian will flag the case with the study endocrinologist. The overseeing endocrinologist will then make a decision to either (a) continue until the next review (14 days); (b) refer them to their nominated HCP or GP for independent review; or (c) refer them to the study diabetes educator or study physician for review. If [name] is unavailable, then [name] will be consulted to review the case. All cases referred will be documented and used to assess safety of the intervention in the data analysis and reporting. Participants with hypo unawareness will be excluded from participating in the study. However, if any participant believes they might have developed hypo unawareness during the study, they will be advised to contact [name] (study dietitian) as soon as possible, who will flag the case with the study endocrinologist to be assessed on an individual basis.

### **7.3.3 Dehydration or sodium deficiency (including hyponatraemia)**

Due to the expected lowering of insulin requirements and circulating blood insulin in participants adhering to the LC diet, there is a risk of sodium deficiency or dehydration given insulin's role in sodium retention and sodium's role in fluid retention. Hyponatraemia is defined as a serum sodium concentration  $<135$  mEq/L [28]. Although sodium requirements are increased on a LC diet, the diet is also expected to improve blood glucose control, and given that hyperglycaemia is a cause of hyponatraemia in individuals with diabetes [29], we expect the absolute risk of hyponatraemia to be low. Nevertheless, a resource titled, 'Importance of Sodium & Hydration' (Attachment 51) will be provided to participants at the beginning of the intervention period to provide specific instructions on minimising the risk of developing hyponatraemia and/or dehydration. To mitigate this risk, sodium recommendations will be increased relative to the Suggested Dietary Target (2000 mg/day) to 3000-6000 mg/day. Participants will

also be provided with the recommend amount of salt (provided as sealed salt pouches) and instructed to measure out 1.5 tsp and add to food and drink over the course of each day. In addition, minimally processed foods that contain sodium, such as cheese, olives, pickles and canned fish, will be recommended.

Participants will also be monitored throughout the study. Serum sodium levels will be measured at three time-points throughout the study (1. pre-control period, 2. post-control period/pre-intervention period, 3. post-intervention period) (Section 9.3). If a participant is detected to have mild hyponatraemia (serum sodium concentration 130-134 mEq/L [30]) measured at any time point throughout the study, the study physician will provide an immediate assessment of the patient (via Telehealth) and advise the patient and study dietitian on what steps need to be taken (e.g., increasing sodium intake, reviewing medications, etc.). In cases of moderate or severe hyponatraemia (<130 mEq/L [30]), the participant will be contacted immediately and advised to seek emergency medical treatment. Symptoms that may indicate a greater need for salt will be monitored by the study dietitian at each diet session (once a fortnight) and include cold extremities, dark urine, dry mouth, postural dizziness, salt cravings, thirst, muscle cramps, constipation, light-headedness, low energy and headaches. If a participant reports one or more symptoms as being “moderate” or “severe” in intensity or frequency, the dietitian will advise them to increase their daily intake of salt by half a teaspoon and encourage them to drink water to thirst. A similar approach was used in a larger clinical trial investigating ketogenic diets (<30 g/day) in patients with type 2 diabetes (n=262) [23]. If a participant reports one or more symptoms as being “severe” in intensity or frequency, the dietitian will also flag the case with the study physician and a medical assessment will be organised for the participant if deemed necessary.

